#### Subject Selection

The subjects will be recruited from the community pool of substudy 1 and the institutional pool. The eligibility based on inclusion and the investigators will assess exclusion criteria. The institutional pool, which comprises the women attending endocrinology, gynecology, or other clinics for various complaints suggestive of PCOS, will be taken for purposes of recruitment in the intervention part of phase 1 or for further assessment in forming a long-term cohort. Potentially eligible patients will be recruited from the outpatient department services of the participating centers. If the subjects qualify on the inclusion and exclusion criteria, they will be informed about the details of the study and hence will be approached for written informed consent. All potentially eligible patients will undergo clinical, biochemical, and imaging (US) assessment to confirm PCOS. A logbook will be maintained for all patients undergo screening, randomized, eligible but not randomized along with reasons for non-randomization. For the intervention study (substudy 3), the subjects will be recruited only from AIIMS, New Delhi, and SKIMS, Srinagar. The sleep study and carotid Doppler at SKIMS and AIIMS, New Delhi, will be conducted for 100 subjects at each site.

The drug-naïve women who qualify on the 1990 NIH criteria (from both the institutional pool and the community pool) will be invited for the study. This will be an open-label randomized intervention trial and will follow a common protocol at each participating center. Women who do not desire fertility and who furnish written informed consent (second time) will undergo a detailed clinical assessment including details of menstrual, drug, and other relevant history followed by clinical examination involving anthropometry (height, weight, waist circumference); Ferriman-Gallwey scoring for hirsutism; grading of acanthosis nigricans, androgenic alopecia, and acne vulgaris (grades 1-3); blood pressure measurement; and a brief relevant systemic examination. Biochemical and hormone estimation will be done at baseline from the second day to the seventh day of the menstruation cycle and at 3 and 6 months. The subjects will be followed up at 6 months, and all these investigations will be repeated at the follow-up. A total of 320 women for the intervention phase (ie, 80 subjects per arm and per center) will be recruited. The study will be done only in 2 participating centers (SKIMS, Srinagar, and AIIMS, New Delhi). The intervention phase will be initially done for a period of 24 weeks.

#### Baseline Assessment

Standardized study tools will be used to record patient name, contact details, history, family history, personal information (age of menarche, menstrual regularity information, acne severity), food habits, lifestyle habits, previous disease information, drug intake history information, and clinical details including anthropometry (height, skinfold, waist circumference) by using anthropometric tools (SECA 213 height scale, SECA 813 weight scale, SECA 203 nonstretchable tape, and calipers measuring skinfold thickness), blood pressure (using Omron blood pressure instruments), Ferriman-Gallwey score, androgenic alopecia, acanthosis nigricans, acne vulgaris, and systemic examination. Measurement of biochemical parameters (blood glucose, OGTT, lipid profile, liver function, kidney function), protein:creatinine ratio, and 25OHD (in selected cases); hormonal assays (like T_4_, thyrotropin, LH, FSH, PRL, E2, P4—21st day optional, cortisol, testosterone, AMH, DHEAS, 17OHP, SHBG, and insulin); and radiological assessment will be done at baseline and after 6 months of treatment.

#### Follow-Up and Safety Evaluation

Patients will be evaluated for any adverse events and efficacy at 90 days (−7 days to +7 days) and 180 days (−7 days to +7 days) through follow-up. All clinical and biochemical investigation will be performed in a similar fashion as done at baseline. If the patient is not available for assessment at 180 days (−7 days to +7 days) follow-up, this will be considered a protocol deviation. The safety of different interventions will be assessed by recording the development of immediate or delayed complications recorded in a form with a prespecified list of safety parameters. Immediate reactions will include allergic reactions, diarrhea, vomiting, deep vein thrombosis, etc in a prespecified checklist.

#### Field Activities

Field activities will be conducted for the purposes of screening. It will include rapport building among locals and the selection of the study subjects (1 woman per household). It will be the duty of the research staff to approach the selected individuals and to make them understand their role in the study. Consenting individuals will be screened for PCOS phenotype using the predesigned structured questionnaire. The screening questionnaire will be used to obtain information on personal identification details, demographics, socioeconomic status, menstrual history and clinical information, history of any systemic disease, and QOL. The women who have hyperandrogenism or oligomenorrhea with or without obesity and acanthosis nigricans (IR) will be taken as probable cases of PCOS. Screen-positive and selected screen-negative (regular menstrual cycles, no features of hyperandrogenism or insulin resistance) individuals will be informed to visit the hospital for further investigations.

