**Figure 2 figure2:**
[figure not shown]
Flowchart for sampling design and workflow of the study. AE-PCOS: Androgen Excess and Polycystic Ovary Syndrome; AIIMS: All India Institute of Medical Sciences; GMC: Government Medical College; IPGMER: Institute of Post Graduate Medical Education & Research; MHRT: Maternal Health & Research Trust; NEIGRIHMS: North Eastern Indira Gandhi Regional Institute of Health and Medical Sciences; NIH: National Institutes of Health; NIRRH: National Institute for Research in Reproductive Health; OMC: Osmania Medical College; PCOS: polycystic ovary syndrome; PGIMER: Postgraduate Institute of Medical Education and Research; SKIMS: Sher-i-Kashmir Institute of Medical Sciences.

#### Estimation of Sample Size for Substudy 1

Sample size was calculated, primarily to estimate the prevalence of PCOS in the country. Previously reported prevalence rates of PCOS have varied from 3.7% to 22.3% [32,33]. For the purpose of calculation of sample size, we presume the prevalence of PCOS in India to be 10%. With an assumed prevalence of 10% and an absolute error margin of 1% in a 95% 2-sided confidence interval and making allowance for about 20% refusals or nonresponse, we need to target a total of 4500 women. Further, being a cluster design and taking a design effect of 2, a total of 9000 women aged 18-40 years will be studied from 10 centers (ie, 1000 per center, except for the 2 centers in Hyderabad, which have been designated with 500 each), half from a rural community and half from an urban community at each center.

Based on a pilot study previously conducted by the chief coordinator using a similar questionnaire [34], 30% (2700/9000) of the women are expected to screen positive (likely to have PCOS) on the screening questionnaire and therefore are required to be investigated in detail. Additionally, of the 70% (6300/9000) of women expected to screen negative on the screening questionnaire, 20% (1260/6300) will require examination and investigation in detail. This will make the sample size of women requiring detailed evaluation and blood testing a total of 3960 (N=2700+1260). Keeping in view the number of centers (N=10), each participant center will screen approximately 1000 women, and a total of 440 women who will be invited for detailed examinations: 20% (140/700) of screen-negative women and all 30% (300/1000) who screen positive (Figure 2).

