### Study Tool: The Questionnaire

In this study, structured questionnaires will be used for capturing information. The eligibility and screening questionnaires comprise 7 and 43 questions (part 1), respectively. The screening questionnaire comprises three sections: (1) personal details, (2) menstrual history and clinical information, and (3) history of any systemic diseases. Part 1 of the questionnaires will be filled at the field site to check eligibility and identify probable PCOS on the basis of positive responses to questions. The subjects who test positive on the questionnaire (ie, probable PCOS) and 20% of those who test negative (healthy women) will be invited to the respective institutes for detailed clinical assessment. The questionnaire stands pilot-tested and modified after several rounds of investigator meetings.

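### As worded, the field rule leaves women with only insulin-resistance features neither screen-positive nor eligible for the screen-negative examination, contradicting the 30%/70% split and the 20% sample of all negatives

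*Protocol article*

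**What the plan says.** Three sections of the protocol article describe who goes on to detailed examination in substudy 1.

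- **Field Activities** defines the positive screen: "The women who have hyperandrogenism or oligomenorrhea with or without obesity and acanthosis nigricans (IR) will be taken as probable cases of PCOS". Insulin-resistance signs may accompany the picture but do not make a woman positive on their own. The same section describes the negatives who are sent on: "selected screen-negative (regular menstrual cycles, no features of hyperandrogenism or insulin resistance) individuals will be informed to visit the hospital".
- **Estimation of Sample Size for Substudy 1** expects that "30% (2700/9000) of the women are expected to screen positive" and that "of the 70% (6300/9000) of women expected to screen negative on the screening questionnaire, 20% (1260/6300) will require examination". Per center of 1000 women this is "20% (140/700) of screen-negative women and all 30% (300/1000) who screen positive".
- **Study Tool: The Questionnaire** says that "20% of those who test negative (healthy women) will be invited to the respective institutes for detailed clinical assessment". It attaches no condition about insulin resistance beyond the label in brackets.

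The precision target for the national estimate is stated as follows: "With an assumed prevalence of 10% and an absolute error margin of 1% in a 95% 2-sided confidence interval".

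**The concern.** The two descriptions in Field Activities do not cover everyone. A positive needs one of two features; an examined negative must lack those two and a third. A woman with, say, acanthosis nigricans but regular cycles and no hyperandrogenism fits neither description.

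This matters because examining a sample of negatives is how a two-stage survey counts the cases that its questionnaire misses. If part of the negative group has no chance of examination, weighting cannot recover its missed cases, because no woman from that part is in the sample to carry a weight. If that part also has more undetected PCOS than the rest, the prevalence estimate is too low, and a larger survey does not remove the error.

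There is a practical risk as well. With ten centers, some could follow the field description and others the sample-size section, so the examined negatives would differ in kind between regions whose results are to be compared.

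**Working it through.** **1. The plan's own figures.** Inputs from the sample-size section: prevalence 10%, margin 1 point, 95% confidence, 20% nonresponse, design effect 2.

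- With the normal quantile rounded to 2: 2² × 0.10 × 0.90 / 0.01² = 3600; 3600 / 0.80 = 4500; 4500 × 2 = 9000. This reproduces the stated totals. With 1.96 the chain is 3457, 4322 and 8643.
- Second stage: 0.30 × 9000 = 2700; 0.70 × 9000 = 6300; 0.20 × 6300 = 1260; 2700 + 1260 = 3960. Eight centers of 1000 and two of 500 equal nine full centers, and 3960 / 9 = 440, as stated.

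Because 2700 + 6300 = 9000, the plan counts every woman who is not positive as negative. No third group exists in these figures.

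**2. The field rule set against them.** Let g be the share of the 6300 non-positive women who have only insulin-resistance features. The article gives no value, so 10–30% is assumed.

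| g | women with only these features | expected in a 20% sample of all negatives | examined under the field rule |
|---|---|---|---|
| 10% | 630 | 126 | 0 |
| 30% | 1890 | 378 | 0 |

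If 20% is taken only from the remaining negatives, the count falls short of 1260: 0.20 × (6300 − 630) = 1134, or 0.20 × (6300 − 1890) = 882. The field rule and the sample-size section therefore cannot both be followed unless g is zero.

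**3. Effect on prevalence.** Let q1 and q0 be the rates of undetected PCOS in non-positive women with and without insulin-resistance features.

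- True contribution of the negatives: 0.70 × [g × q1 + (1 − g) × q0].
- Contribution if the rate in the examined negatives is applied to all: 0.70 × q0.
- Understatement: 0.70 × g × (q1 − q0).

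q1 and q0 are not in the article either. With an assumed excess q1 − q0:

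| g | excess | understatement |
|---|---|---|
| 10% | 0.5 points | 0.70 × 0.10 × 0.5 = 0.035 points |
| 10% | 2 points | 0.14 points |
| 20% | 2 points | 0.28 points |
| 30% | 3 points | 0.70 × 0.30 × 3 = 0.63 points |

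To reach the 1-point margin at g = 30%, the excess would have to be 1 / (0.70 × 0.30) = 4.8 points; at g = 10% it would have to be 14.3 points.

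**4. Which case definition.** Under Evaluation Methods, the qualifying NIH 1990 criteria need both ovulatory dysfunction and hyperandrogenism. A woman who reports regular cycles and shows no hyperandrogenism can be a missed NIH case only if her cycles were misreported and she also has biochemical or unreported hyperandrogenism. The excess is therefore likely to be near the low end. Under the Rotterdam and AE-PCOS criteria, used for comparison, biochemical hyperandrogenism plus polycystic ovaries on ultrasound is enough, even with regular cycles. A field questionnaire shows neither, so the excess can be larger there.

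**The case against.** The strongest reply is that the bracketed words in Field Activities are a loose description of a screen-negative woman and not an eligibility rule. The two sections that fix the 20% fraction apply it to all who test negative, and the questionnaire's scoring is not shown. If the scoring places women with only insulin-resistance features in one group or the other, none is left out. This may well be the intention. But Field Activities is the section that describes what staff do, and the questionnaire section's label of negatives as healthy points the same way. The contradiction on the page stands, and one sentence would settle it.

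It is also fair to say that the article does not state how examined negatives enter the prevalence estimate, and that an analysis plan may do so. The bias is therefore conditional on the field rule being applied and on the result being extended to all negatives.

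Two stronger readings are tempting and are not supported:

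- A reader might infer that the PCOS-versus-healthy comparison of comorbidities is distorted. The abstract and Primary Objectives describe the comorbidity burden among women with PCOS, and Statistical Analysis speaks of comparing groups without naming them. No comorbidity contrast with screen-negative women is stated. Only if these women serve as non-PCOS comparators, for example for risk factors related to insulin resistance, would such a contrast be exaggerated.
- A reader might infer from the word selected that the negatives are hand-picked. The word does not establish that, and a condensed article can leave the mechanism of the draw to the full protocol.

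**Conclusion.** The inconsistency is real and should be corrected. As written, the field description gives women with only insulin-resistance features no route to examination, while the sample-size and questionnaire sections require a sample of all negatives.

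The consequence for prevalence is conditional. It needs the field rule to be applied, the examined negatives' rate to be extended to all 6300, and undetected PCOS to be more frequent in the omitted women. On assumed values (g 10–30%, excess 0.5–3 points) the understatement is about 0.04–0.63 points. That lies inside the planned 1-point margin but adds to it as a one-sided error. It is probably near the lower end for the NIH estimate and can be larger for the Rotterdam and AE-PCOS estimates. The article does not show that a material bias will occur, nor that any comorbidity comparison is affected.

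**What to change.** - Reconcile Field Activities, Study Tool: The Questionnaire and Estimation of Sample Size for Substudy 1 by defining screen-negative as every screened woman who is not screen-positive.
- Draw the planned 20% at random from that complete list, separately within each center's urban and rural lists.
- In the prevalence estimate, weight the examined negatives by the inverse of their sampling fraction (planned weight 1 / 0.20 = 5, so 1260 × 5 = 6300).

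Made before or during field work, this costs one reworded rule and a random draw; the 1260 examinations and the total of 9000 do not change.

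The Results section puts the start of recruitment in 2018 and its expected end in October 2021, so field work may already be complete. If the field rule was applied, recalling 20% of the omitted women would mean 126–378 hospital work-ups on the assumed range of g, which is not a small request. It is enough then to report how many screened women had only insulin-resistance features and were not eligible for examination, and to give a sensitivity range for prevalence using the formula above, separately for each set of diagnostic criteria.

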### Statistical Analysis

Data will be collected on predesigned proformas. The data obtained will then be entered using pilot-tested CSPro software (version 6.2; United States Census Bureau). After assessing for approximate normal distribution, all continuous variables will be summarized as mean (SD) or median (IQR). Categorical variables will be expressed as n (%). Student *t* test and analysis of variance will be used to compare the groups. Statistical analysis will be performed using reliable SPSS statistical software (version 26; IBM Corp).

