#### Laboratory Evaluation

The OGTT will be performed after an overnight fast of 10-12 hours. An oral glucose load with 75 g of anhydrous glucose dissolved in 250-350 mL of water will be administered over 3-5 minutes immediately after the basal sample. The blood samples for LH, FSH, testosterone, AMH, SHBG, and DHEAS will be collected on days 3-7 (early follicular phase) of spontaneous or medroxyprogesterone-induced (in amenorrhea patients) menstrual cycle to confirm PCOS. Hematological parameters (hemoglobin, red blood cells, white blood cells, etc), biochemical tests like lipid profile, liver function, kidney function, blood glucose (OGTT), and hormonal assays like T_4_, thyrotropin, LH, FSH, PRL, E2, P4, cortisol, testosterone, AMH, DHEAS, 17OHP, and insulin at 0 hours, 30 minutes, and 2 hours (optional) will be carried out at the respective centers, and special hormones like testosterone and SHBG will be done in the central facility to be created at the coordinating center (SKIMS, Srinagar). On the day of testing, women will be called after 10-12 hours of fast, and blood samples (15 ml) will be drawn. Blood will be also collected for glucose and insulin estimation after 30 minutes and 120 minutes of 75 g oral glucose challenge. Insulin samples will be immediately put in a refrigerator, separated in cold centrifuge, and stored at −20 °C until the assay. Plasma will be separated in a refrigerated centrifuge at 1560*g* for 10 minutes, and sera will be stored at −80 °C until tested.

Plasma glucose will be measured using the glucose oxidase–peroxidase method, and hormonal tests (LH, FSH, T_4_, thyrotropin, PRL, E2, cortisol, testosterone, AMH, hsCRP, cytokines, and 25OHD) will use ECLIA on Cobas e411 (Roche Diagnostics USA).

### Methodology: Protocol for Substudy 3

The study will be conducted only at 2 centers: AIIMS, New Delhi, and SKIMS, Srinagar. Women (aged 18-40 years) residing in the communities (rural and urban) identified in the prevalence study and those attending outpatient clinics in the departments of either endocrinology, gynecology, or dermatology of the selected institutes who are willing to participate will be recruited in the interventional part of the study. All these women will undergo clinical, biochemical, and hormonal assessment at baseline and at 3 and 6 months (Figure 4).

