**Figure 4 figure4:**
[figure not shown]
Study design and workflow chart of substudy 3. 17-OHP: 17-hydroxyprogesterone; AMH: anti-Müllerian hormone; BP: blood pressure; DHEA-S: dehydroepiandrosterone sulfate; FG: Ferriman-Gallwey; FSH: follicle-stimulating hormone; LH: luteinizing hormone; OCP: oral contraceptive pill; OGTT: oral glucose tolerance test; PCOS: polycystic ovary syndrome; PRL: prolactin; SHBG: sex hormone–binding globulin; T4: thyroxine; TSH: thyrotropin.

#### Sample Size Calculation for Substudy 3

On the basis of one study, metformin could improve the Homeostatic Model Assessment of IR from 2.5 (SD 0.39) to 2.79 (SD 0.39) [38]. Assuming that the baseline was similar, at an α error of 0.05 with power of 90%, and with a projected attrition rate of 20%, we need to recruit 153 women per group. To round off, we will recruit and randomize 160 women with PCOS per group (ie, a total of 320 women). A total of 160 subjects will be recruited and randomized in each of the 2 groups, with 80 subjects in each arm.

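### Substudy 3: replace the named t test/ANOVA with ANCOVA adjusted for baseline HOMA-IR and centre, a free gain in precision rather than the repair of an invalid test

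*Protocol article*

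**What the plan says.** The Statistical Analysis section covers all three substudies with one sentence on comparisons: Student "test and analysis of variance will be used to compare the groups". It names no covariate, centre term, endpoint or time point.

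The rest of the article describes a design with useful baseline information:

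- **Outcome.** Sample Size Calculation for Substudy 3 rests on HOMA-IR: "metformin could improve the Homeostatic Model Assessment of IR from 2.5 (SD 0.39) to 2.79 (SD 0.39"). It continues "at an α error of 0.05 with power of 90%, and with a projected attrition rate of 20"%, and it takes baselines to be alike ("Assuming that the baseline was similar").
- **Baseline data.** The Baseline Assessment section lists blood glucose and insulin, from which HOMA-IR is formed.
- **Centre.** Subject Selection fixes recruitment at "80 subjects per arm and per center", with two centres. Randomisation is 1:1. Stratification by centre is not stated.
- **Visits.** Methodology: Protocol for Substudy 3 says "All these women will undergo clinical, biochemical, and hormonal assessment at baseline and at 3 and 6 months". Subject Selection and the Follow-Up and Safety Evaluation section agree with that. The Baseline Assessment sentence that lists glucose and insulin gives only baseline and after 6 months.

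**The concern.** A t test or one-way ANOVA leaves in the error term all the between-woman variation in HOMA-IR that was already present before treatment. When the outcome is also measured at baseline, part of that variation is predictable and can be removed without recruiting anyone. Chance baseline differences between arms are then corrected in the estimate itself; an unadjusted test only allows for them in the standard error.

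Precision is what is at stake. Wider intervals matter most if the true effect is smaller than the 0.29 used for planning, or for the other continuous outcomes, for which the article gives no sample size calculation.

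**Working it through.** **Inputs.** From Sample Size Calculation for Substudy 3: difference 2.79 − 2.5 = 0.29 (only its size is used here), SD 0.39, α 0.05 (taken as two-sided), power 90%, attrition 20%. From Randomization (Drug Intervention): each comparison of drug plus lifestyle with lifestyle alone has 160 women, so 80 per treatment and 80 × 0.8 = 64 evaluable. The correlation r between baseline and 6-month HOMA-IR is not in the article; 0.3, 0.5 and 0.7 are assumed.

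**1. The plan's own figure.** n per group = 2 × [0.39 × (1.960 + 1.282) / 0.29]² = 38.0, taken up to 39; with attrition 39 / 0.8 = 49. The article says "we need to recruit 153 women per group". That figure does not follow from the stated inputs. This is a separate matter, but it means that the intended effect is uncertain, so step 5 tries both readings.

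**2. Variance factors for baseline-adjusted ANCOVA.** With equal SDs σ at baseline and 6 months, the residual variance is
- t test on 6-month values: σ²
- t test on changes: 2(1 − r)σ²
- ANCOVA: (1 − r²)σ²

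The ratio of ANCOVA to the first is 1 − r². The ratio to the second is (1 − r²) / [2(1 − r)] = (1 + r)/2.

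| r | vs 6-month t test | vs change-score t test |
|---|---|---|
| 0.3 | 0.91 | 0.65 |
| 0.5 | 0.75 | 0.75 |
| 0.7 | 0.51 | 0.85 |

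The article does not say which t test is meant, so both columns are needed.

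**3. The same gain as extra women per treatment,** 64 × (1/factor − 1): 6, 21 and 61 against the 6-month t test; 34, 21 and 11 against the change-score test.

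**4. Detectable difference at 90% power, 64 per treatment.** (1.960 + 1.282) × 0.39 × √(2/64) = 0.223 for the 6-month t test. Multiplying by √(1 − r²) gives 0.213, 0.194 and 0.160. With 128 evaluable per group (160 × 0.8, if two groups of 160 are compared), the figures are 0.158, then 0.151, 0.137 and 0.113.

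**5. Power at 64 per treatment.**

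| Assumed effect | 6-month t test | ANCOVA, r = 0.3 / 0.5 / 0.7 |
|---|---|---|
| 0.29 with SD 0.39, as stated | 98.8% | 99.3 / 99.8 / >99.9% |
| 0.414 SD, as implied by 153 per group less 20% | 65% | 69 / 77 / 91% |

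**6. Simulation** (3,000 runs, 64 vs 64, equal correlations, true difference 0.29 at both 3 and 6 months, no centre effect). The standard error is 0.069 unadjusted and 0.066 / 0.060 / 0.049 with baseline, with the estimate unbiased. Adding centre to the baseline-adjusted model costs nothing visible.

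**7. The 3-month value as a covariate.** In the same set-up the coefficient of the 3-month value is r/(1 + r), so the estimated effect becomes 0.29 × [1 − r/(1 + r)] = 0.29/(1 + r) = 0.223, 0.193 and 0.171. The simulation agrees (0.22 / 0.20 / 0.17), and power falls from about 99% to 89 / 88 / 91%.

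**The case against.** The strongest reply is that the sentence is generic, written for an umbrella study in a condensed article, and that a full protocol or analysis plan may give the model. Silence on analysis sets, time points and missing data is therefore no fault. Analysis of variance could also include a centre factor. All of that stands. What remains is that the article does name tests for comparing groups, and neither uses the continuous baseline value.

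The reply on power also stands: on the article's own effect and SD there is almost nothing to gain. So does the point that the size of the gain depends on an assumed r and on which t test it is compared with.

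Four stronger readings are tempting and lack support:

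- **That the planned test is biased or invalid.** Under randomisation an unadjusted comparison is unbiased, and its standard error already allows for chance imbalance. The remark about similar baselines belongs to the sample size calculation and is not a premise of the analysis.
- **That the plan analyses only women seen at 6 months and discards 3-month data.** No section says so. Follow-Up and Safety Evaluation calls a missed 180-day visit a protocol deviation and does not remove the woman from analysis.
- **That everything measured should be adjusted for, including 3-month HOMA-IR.** That value is measured after randomisation and carries part of the treatment effect (step 7).
- **That community and clinic women differ greatly.** Subject Selection requires both to be drug-naïve and to meet the same NIH criteria; no figures show a difference.

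**Conclusion.** The point holds as an improvement in efficiency and not as an error. Baseline adjustment lowers residual variance to 0.91, 0.75 or 0.51 of that of a 6-month t test, or to 0.65, 0.75 or 0.85 of that of a change-score t test, for r of 0.3, 0.5 or 0.7. On the stated inputs the benefit is mainly narrower intervals. Power would improve materially only if the real target is nearer the smaller effect implied by 153 per group.

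This rests on the assumed correlations, equal SDs at the two times and 64 evaluable women per treatment. The gain from a centre term cannot be estimated, because nothing shows how strongly centre predicts HOMA-IR and stratified randomisation is not stated. The term is sensible because recruitment is fixed by centre.

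**What to change.** 1. State the substudy 3 comparison as ANCOVA on 6-month HOMA-IR (log scale if skewed) between randomised treatments, adjusted for baseline HOMA-IR and centre. Recruitment source (community or clinic) may be added as a further baseline covariate.
2. Reconcile the Baseline Assessment section with the other three places on whether glucose and insulin are measured at 3 months.
3. If they are, use a mixed model for repeated measures, with the 3- and 6-month values as outcomes, baseline and centre as covariates, and a treatment-by-visit term; report the 6-month contrast. State that the 3-month value is not used as a covariate. If they are not measured at 3 months, the ANCOVA stands alone.

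The cost is analysis wording only. The baseline measurements are already planned, SPSS 26 fits these models, and no extra women are needed. A few degrees of freedom are spent.
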